## Discussion

To the best of our knowledge, this is the first RCT to test the effectiveness of a model combining brief SC advice and active referral smoking cessation intervention in the community setting. Unlike recruiting smokers in the clinical setting where smokers may be more motivated by the undesirable health condition, recruiting smokers in the community may be more difficult. Brief SC advice and referral provided by physicians and other healthcare professionals in the clinical setting has been found effective [27, 28], our study leads to deliver SC advice and refer smokers to SC services by training the university students and volunteers from the NGOs, which is cheaper than health care professionals. This study is unique in several ways. We will refer smokers not only to the SC quit-lines but also to the SC clinics (Western and Traditional Chinese Medicine) upon smokers’ preference. Such strategy allows smokers to choose a service that they believe to be most useful and hence shall increase their adherence to the service. We will evaluate the effectiveness of the intervention not solely by the abstinence rate, but also assessing smokers’ substantial use of referred service and their comments over the service.

If the intervention is proven feasible and effective in SC, it could ease the burden made by smoking on the medical system as the referral and SC advice are not necessarily to be done by healthcare professionals and hopefully result in less medical cost on diseases that are attributed to smoking. The study will also demonstrate the importance of partnership between SC services on the promotion of SC in the community.

### Ethical approval and consent

This study has received ethical approval by the Institutional Review Board of the University of Hong Kong/ Hospital Authority Hong Kong West Cluster (IRB reference no.: UW15-332). The study poses minimal additional risk to study participants. Informed consent will be obtained from the participants for their participation in the study and agreement to allow us to transfer their contact information to their chosen SC service providers (for Group A only).

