**Methods/Design:**

This is a single-blinded, parallel three-armed cluster randomized controlled trial (RCT) with two treatment groups of (1) brief SC advice using the AWARD model, active referral to SC services plus a referral card and a health warning leaflet (active referral group) and (2) brief SC advice using AWARD model and health warning leaflet (brief advice group) and a control group receives general very brief advice with a self-help booklet. A total of 1291 smokers will be recruited from 66 clusters (recruitment sessions) with 22 will be allocated to each of the two intervention and one control groups. SC ambassadors will be trained for delivering the interventions and conducting telephone follow-up. The primary outcomes are self-reported 7-days point prevalence (PP) abstinence at 3 and 6 months follow-up. Intention-to-treat principle and multi-level regressions will be used for data analysis.

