### Recruitment

Participants will be recruited over 3 months from 66 recruitment sessions in the community in all 18 districts in Hong Kong as in our previous “Quit-to-Win” project [19, 22, 23]. Public open places with high flow of smokers will be identified and these mostly include outdoor places near large shopping malls or housing estates. Booths containing SC and recruitment messages will be set up onsite to attract smokers. Well-trained SC ambassadors will actively recruit the smokers who are near or attending the booths. The SC ambassadors are trained university students (mainly from the fields of nursing, public health, science and social sciences) and volunteers from the non-governmental organizations (NGOs). The SC ambassadors have to attend a two-day workshop in which they learnt the basic knowledge on smoking, tobacco control, SC services, skills on recruitment and intervention delivery. We will adopt “a-foot-in-the-door” approach [24] by asking the smokers their interests on participating in the SC trial. Smokers who showed interests will be assessed for eligibility and informed consents will be sought. The study has been approved by the Institutional Review Board of the University of Hong Kong/Hospital Authority Hong Kong West Cluster (UW15-332) and registered at ClinicalTrials.gov (NCT02539875).

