### Cluster randomization

All participants recruited in a particular recruitment activity will be allocated to one of the 3 RCT groups. Individual randomization will not be used as the risk of intervention contamination at each site is high. Cluster randomization will be used to ensure the number of recruitment activities for the three RCT groups is similar. Sixty-six recruitment activities will be randomly assigned to any one of the three RCT groups by randomly generating blocks of 3, 6 or 9. The investigator will generate a list of random numbers in each block using Microsoft Excel. The list of random numbers will be assigned to a list of group assignment in which the first, second and third tertile will be as the active referral, brief advice and control groups respectively. A co-investigator who is not aware of allocation group will subsequently sort the random number in each block and that will be the group assignment sequence of the recruitment activities.

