### Blinding

The RCT is single-blinded that all outcome assessors are not aware of the group assignment of the subjects.

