#### Active referral

Subjects will receive a referral card and be actively referred to one of the five major SC services in Hong Kong, including (1) Department of Health SC Services, (2) Tung Wah Group Hospital Integrated Center on SC, (3) Hospital Authority (HA) SC Clinics, (4) Pok Oi Hospital Chinese Medicine SC Services, and (5) University of Hong Kong Youth Quit-line. The details of each service are shown in Table 2. The well-trained SC ambassadors will explain the SC services to the subjects who will be asked to choose one of the SC services to be referred. Informed written consent and contact telephone number of the subjects will be obtained at the recruitment site, processed primarily in the university research office (including putting subjects’ information into computer), transferred to the collaborator - COSH (Hong Kong Council on Smoking and Health) and eventually destined at the selected service provider within 7 days. As proactive phone call service is not available in HA Clinics, subjects will be encouraged to make the appointment by themselves using a provided list of HA clinics contact addresses and telephone numbers. Research staff will monitor SC services use of the subjects and assist them to make or re-make the appointment if necessary in each follow-up (1-, 2-, 3- and 6- month).

**Table 2 Tab2:** Major smoking cessation services in Hong Kong

	Main services
Department of Health	Phone SC counselling managed by registered nurses.
Hospital Authority	SC clinics run by physicians and nurses.
	Free nicotine replacement therapy (NRT) and cessation drugs.
Tung Wah Group of Hospitals	SC clinics run by physician, nurses, and social worker.
	Free nicotine replacement therapy (NRT) and cessation drugs.
Pok Oi Hospital	SC clinics run by Chinese medical practitioners.
	Free acupuncture cessation therapy.
Youth Quit-line	Telephone counselling by well-trained youth smoking cessation counsellors.

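### Smokers are screened and consented after their session's arm is fixed, and only active-referral consent covers contact transfer, so that arm may differ in motivation from the others

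*Protocol article*

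**What the plan says.** **Allocation.** The Cluster randomization section assigns arms to 66 sessions, not to people: "All participants recruited in a particular recruitment activity will be allocated to one of the 3 RCT groups". The sorted random list gives an order of arms, and "that will be the group assignment sequence of the recruitment activities".

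**Recruitment.** The Recruitment section then describes what happens on the day: "Well-trained SC ambassadors will actively recruit the smokers who are near or attending the booths", followed by "Smokers who showed interests will be assessed for eligibility and informed consents will be sought".

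**Delivery and blinding.** The abstract says that "SC ambassadors will be trained for delivering the interventions and conducting telephone follow-up". The Active referral section has ambassadors explain the services and ask the subject to choose one. The Blinding section covers outcome assessment only: "The RCT is single-blinded that all outcome assessors are not aware of the group assignment of the subjects".

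**Consent.** The Ethical approval and consent section requires consent to participate in every arm and adds "agreement to allow us to transfer their contact information to their chosen SC service providers (for Group A only". Group A is evidently the active referral group. The Active referral section places this on site: "Informed written consent and contact telephone number of the subjects will be obtained at the recruitment site".

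**The concern.** Randomising sessions balances places and days. It does not balance who joins once the session's arm is set. If the people who invite and screen smokers know the arm, or if one arm asks for something extra at consent, the enrolled groups can differ before treatment starts.

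Both routes are open here. A smoker's wish to stop or cut down is an eligibility criterion that calls for judgement, and ambassadors apply it. Agreement to have one's details passed to a cessation service is asked in one arm only, and it is plausibly related to motivation to quit.

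Two of the three main comparisons involve active referral. The comparison with brief advice matters most, because it isolates the trial's new component and the brief-advice consent has no matching element.

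**Working it through.** **1. Order of events.** Read together, the sections give this sequence: session allocated; smoker approached; eligibility assessed; consent sought; intervention delivered. The first step precedes all individual contact. No section describes a step that keeps the session's arm from the recruiters until consent is complete. The co-investigator who is unaware of allocation only sorts the list.

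**2. What is not stated.** The article does not say when ambassadors learn the arm. That they know it beforehand is an inference from one arm per session, arm-specific materials and arm-specific consent. It also does not say what happens to a Group A smoker who refuses transfer.

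**3. Size if refusers are not enrolled.** The plan gives no figure for this, so there is nothing to reproduce. Let *p* be the quit rate among all eligible smokers, *f* the share who refuse transfer, and *r* the quit rate among refusers. With no treatment effect, the enrolled active arm shows

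(p − f·r) / (1 − f).

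The value p = 0.10 is the control rate in the Sample-size calculation section. Both *f* and *r* are assumptions.

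Milder set: half of eligible smokers are highly ready, with 2 or 3 times the quit rate of the rest. The less-ready rate is then 0.10/(0.5 + 0.5×2) = 0.0667 or 0.10/(0.5 + 0.5×3) = 0.05. If 10% to 50% of the less ready refuse, f = 0.05 to 0.25. Stronger set: r = 0.05 and f = 0.20 to 0.40.

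| Set | f | r | Null quit rate, active arm | Excess as share of 6 points |
|---|---|---|---|---|
| Milder | 0.05 | 0.0667 | 0.0967/0.95 = 10.2% | 3% |
| Milder | 0.25 | 0.05 | 0.0875/0.75 = 11.7% | 28% |
| Stronger | 0.20 | 0.05 | 0.090/0.80 = 11.3% | 21% |
| Stronger | 0.30 | 0.05 | 0.085/0.70 = 12.1% | 36% |
| Stronger | 0.40 | 0.05 | 0.080/0.60 = 13.3% | 56% |

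The 6 points are the planned 16% minus 10%. The plan sets that difference for the two intervention arms combined against control, so it serves here only as a yardstick.

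**4. Effect on the test, milder set only.** Retained per arm: 1291×0.70/3 = 301. Retained per session: 1291×0.70/66 = 13.7. Design effect: 1 + 12.7×0.005 = 1.063. Effective number: 301/1.063 ≈ 283 per arm. A two-sided 5% test against an arm at 10% would then reject in 5.1% (active arm at 10.2%) to 9.8% (at 11.7%) of trials with no true effect.

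**5. Safeguards in the plan.** Intention-to-treat keeps people in their arm once enrolled; it cannot bring back those who never joined. The multi-level model handles correlation within sessions, not selection. Readiness, importance, difficulty and confidence are measured at baseline, so an imbalance is partly visible. Adjustment is left to judgement, however, and cannot reach motivation that was not measured.

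**The case against.** A reader might infer that, as the plan is written, a smoker who refuses transfer is turned away in Group A but enrolled elsewhere. The documents do not support that. Willingness to be referred is not among the eligibility criteria, and the ethics section names two agreements without making one a condition of the other. The Active referral section mentions written consent while describing the intervention, for people already called subjects. That is compatible with a separate, later signature, and the study-design figure or the consent forms may show the order.

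The hurdle may also be low. Subjects choose among five services, and the Hospital Authority clinics make no proactive calls. All arms share the same broad intent criterion alongside an objective carbon monoxide threshold. A smoker may refuse transfer for reasons unrelated to motivation, so the direction of bias is not certain. The consent element does not touch brief advice versus control.

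All of this stands, and it limits the point to a conditional one. It does not remove it: allocation still precedes individual recruitment, recruiters are still not described as blinded, and one arm's consent still has an extra element whose refusal has no stated consequence.

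**Conclusion.** The concern holds as a risk built into the order of allocation and consent, not as a demonstrated bias. If refusal of transfer means non-enrolment, or if ambassadors recruit differently by arm, the active referral arm may differ in motivation from the other two, probably in its favour.

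The range of 10.2% to 13.3% against 10% rests wholly on the assumed refusal rates, on refusers quitting less often, and on all of them being lost to the trial. It should not be read as an estimate; the upper end in particular has no support in the document. If refusers already stay in Group A, the consent route largely closes and only recruiter behaviour remains.

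This is a worthwhile, inexpensive improvement rather than a fatal flaw.

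**What to change.** - Use one identical trial consent, eligibility check and baseline questionnaire in all three arms, completed before any arm-specific material is introduced.
- In the active referral arm, ask for contact-transfer agreement afterwards, with its own signature, as part of the intervention.
- State that those who decline transfer remain in the active referral arm under intention-to-treat.
- Record the numbers approached, eligible and consented at each session, and compare them by arm.

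This removes selection through the consent form. It makes any remaining selection by recruiters visible but does not eliminate it, since ambassadors may still know the session's arm.

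The cost is a split consent form with an ethics amendment and a tally sheet per session. Some active-arm participants will not be referred, which slightly dilutes the active referral effect. If the full protocol already keeps decliners in the arm, saying so meets the third item at no cost.

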## Abbreviations

AWARD: Ask, Warn, Advice, Refer and Do-it-again
CO: carbon monoxide
CONSORT: consolidated standards of reporting trials
COSH: Hong Kong Council on Smoking and Health
HA: Hospital Authority
HK: Hong Kong
ITT: intention-to-treat
NGOs: non-governmental organizations
NRT: nicotine replacement therapy
PP: point prevalence
RCT: randomized controlled trial
SC: smoking cessation
